## Abstract

**Background:**

Androgen Deprivation Therapy (ADT) for prostate cancer causes significant adverse effects including muscle wasting, bone density reduction, increased fatigue, and psychological distress. Despite growing evidence supporting exercise as an effective countermeasure, standardized evidence-based protocols for this population remain underdeveloped in clinical practice. Exercise is beneficial for managing cancer-related side effects, and general exercise guidelines for cancer survivors are available, but tailoring of exercise interventions may be more effective in those with treatment-specific complications.

**Methods/design:**

This randomized controlled trial with two parallel arms compares a 24-week supervised progressive resistance training program (SPoRT-PCa-ADT) with a control group receiving personalized home-based training following initial assessment and weekly telephone follow-up. The SPoRT-PCa-ADT Program utilizes velocity-based training methodology, progressing through three distinct phases (adaptation, development, maintenance) with intensity corresponding to 60% 1RM (mean propulsive velocity 0.92 m/s) and a 10% velocity loss threshold. The exercise protocol focuses primarily on squat movement patterns with real-time velocity feedback and incorporates daily readiness assessment to accommodate treatment-related fatigue fluctuations. Control group participants receive structured written instructions for home-based resistance training including warm-up and three effective sets of 12 repetitions of box squats, to be performed two to three times per week on non-consecutive days, with weekly telephone monitoring. The comprehensive assessment protocol includes progressive loading tests, vertical jump assessment, isometric strength measurement, and patient-reported outcomes measuring fatigue, quality of life, psychological distress, urinary function, and sleep quality. Assessments occur at baseline, midpoint (patient-reported outcomes only), and post-intervention, with additional biomarker collection.

**Discussion:**

To our knowledge, this will be the first study to implement a standardized velocity-based training protocol specifically developed for prostate cancer patients receiving ADT. The supervised program is delivered by exercise physiologists in a specialized sports center setting with consistent medical oversight, facilitating integration within cancer care pathways while ensuring exercise quality and safety. This detailed randomized controlled trial protocol provides clinicians with a standardized yet adaptable framework for exercise prescription in PCa-ADT patients, bridging the gap between evidence-based exercise principles and clinical implementation.

**Trial registration:**

ClinicalTrials.gov (NCT07064811, protocol version: 1.0, date registered:15 July 2025).

**Supplementary Information:**

The online version contains supplementary material available at 10.1186/s12885-026-15902-w.

## Background

Cancer remains a leading cause of mortality globally, with the World Health Organization reporting an estimated 10 million deaths annually [1]. This complex group of diseases comprises over 200 unique varieties, each presenting distinct challenges regarding management and treatment. The global cancer burden continues to rise, with an estimated 19.3 million new cases in 2020 and projections indicating this will increase to 28.4 million by 2040 [2]. Among the various cancer types, prostate cancer (PCa) represents a significant global health concern as the second most frequently diagnosed cancer in men worldwide. According to Global Cancer Observatory estimates, approximately 1.4 million new cases of PCa were diagnosed in 2020, with incidence rates projected to continue rising, particularly in developed countries [3].

Androgen Deprivation Therapy (ADT) has been established as a cornerstone treatment for advanced PCa, demonstrating considerable success in managing disease progression [4]. This treatment acts through multiple mechanisms to decrease testosterone levels, thereby inhibiting or slowing cancer growth. While effective as a cancer treatment, ADT induces a multifaceted set of adverse effects that substantially impact patients’ quality of life. As Crawford et al. documented [5], ADT-induced hypogonadism causes numerous physiological and psychological sequelae ranging from severe fatigue and muscle wasting to decreased bone density and psychological distress. These side effects typically persist throughout the entire treatment duration, which in many cases may extend for several years.

The physiological effects of ADT have been extensively investigated in the research literature. Smith et al. [6] demonstrated that individuals receiving ADT experience considerable decreases in muscle mass, with losses reaching 3–4% in the first year of treatment. This reduction in lean body mass is accompanied by decreases in strength and power output, variables directly linked to functional independence and quality of life [7]. Longitudinal research has shown that these changes can occur as early as three months following treatment initiation and continue to progress throughout therapy. Additionally, patients typically experience increased fat mass and decreased bone mineral density, making them susceptible to fractures and metabolic disease [8]. Research has demonstrated that bone loss during the first year of ADT can be up to 10-fold higher than bone loss from normal aging in healthy men.

The psychological impact of ADT is equally significant and interconnected with physical changes. A systematic review conducted by Qazi et al. [9] concluded that patients undergoing ADT develop considerable levels of fatigue, depression, sexual dysfunction, and anxiety. This combination of symptoms, also referred to as asthenia, represents a chronic condition of physical weakness and mental fatigue that severely limits patients’ capacity to conduct normal activities and maintain social relationships [10]. The psychological impact extends beyond the individual patient, affecting familial relationships, social connections, and overall quality of life. Research has established that psychological effects can persist even after treatment completion, highlighting the need for integrated support strategies.

Physical exercise has emerged as a promising strategy for reducing the side effects of ADT, supported by several systematic reviews and meta-analyses [11, 12]. Studies have demonstrated that structured exercise programs can preserve muscle mass, protect bone density, decrease fatigue, and enhance psychological well-being in this population. Nevertheless, despite the expanding evidence base, a crucial gap exists in standardized, evidence-based exercise guidelines specifically developed for this population. Although generic exercise recommendations are available for cancer patients [13], the distinct physiological and psychological sequelae experienced by men receiving ADT require more targeted interventions. Current literature demonstrates significant heterogeneity in exercise prescription parameters (e.g., supervised versus unsupervised, frequency, progression strategies), creating challenges for clinicians seeking to implement evidence-based practice [14].

The development of standardized exercise programs for specific clinical populations requires careful consideration of multiple factors, including baseline functional status, treatment-related limitations, and progression parameters [15]. Exercise programs for men receiving ADT must address both the physiological deconditioning and psychological impact of treatment while ensuring safety and feasibility. Previous protocols have demonstrated varied success, yet most lack the specificity and rigorous evaluation methods required for widespread clinical implementation [16]. Of particular importance are considerations regarding the timing of exercise initiation relative to ADT commencement, the balance between resistance and aerobic training components, and strategies for incorporating behavioral support interventions to enhance adherence [17].

Moreover, evaluation of exercise protocols must be supported by robust and standardized assessment methods. Current evaluation practices in this population demonstrate considerable heterogeneity, making cross-study comparisons challenging and hindering the translation of evidence-based treatments [18]. Physical evaluations must account for the unique limitations and risks associated with ADT, while psychological assessments must address the complex relationships between physical and mental health. A standardized assessment protocol would enable more consistent outcome measurement and facilitate better comparison of intervention effectiveness across diverse clinical settings.

Recent advances in exercise prescription methodology, particularly velocity-based training (VBT), offer promising opportunities for optimizing exercise interventions in clinical populations [19]. VBT allows for real-time monitoring and adjustment of training loads based on movement velocity, providing a more individualized and responsive approach to exercise prescription than traditional percentage-based methods. This methodology may be particularly relevant for ADT patients who experience significant day-to-day variations in energy levels and physical capacity due to treatment-related side effects.

Therefore, the purpose of this manuscript is to describe a comprehensive exercise protocol and evaluation system specifically designed for prostate cancer patients receiving androgen deprivation therapy (SPoRT-PCa-ADT). The protocol was developed based on the existing evidence regarding exercise prescription for cancer populations and specifically addresses the limitations associated with patients undergoing androgen deprivation therapy [20]. Furthermore, the evaluation system incorporates validated instruments and standardized procedures, providing a systematic methodology for assessing both physical and psychosocial outcomes in this population. The specific objectives are to: (a) present a comprehensive, evidence-based exercise protocol addressing both physical and psychological consequences of ADT; (b) describe a detailed evaluation methodology for this population; (c) provide explicit implementation guidelines including progression criteria and safety considerations; and (d) establish standardized outcome measures for assessing protocol effectiveness, ultimately bridging the gap between research evidence and clinical practice.

## Methods

### Patient and public involvement

The design of the SPoRT-PCa-ADT trial was informed by the involvement of the Never Surrender Foundation (OncoSport Never Surrender Foundation, Murcia, Spain), a patient advocacy organization dedicated to improving the health and quality of life of cancer patients through exercise-based programs. Representatives of the Foundation participated in the conceptualization of the intervention model, including the selection of the exercise setting, the structure of the supervised sessions, and the design of the home-based control program, ensuring that the protocol reflects the practical needs and preferences of prostate cancer patients undergoing ADT. Additionally, patient perspectives informed the choice of patient-reported outcome measures included in the assessment protocol, prioritizing instruments addressing the symptoms most frequently reported as burdensome by this population, namely fatigue, urinary function, and psychological distress. Patients were not directly involved in the statistical analysis plan or the preparation of this manuscript. Results will be disseminated to participants and the broader patient community through the Never Surrender Foundation upon study completion.

### Design

This randomized controlled trial (RCT) with two parallel study arms evaluates the effectiveness of a 24-week exercise intervention in prostate cancer (PCa) patients undergoing androgen deprivation therapy (ADT). Ethical approval was obtained from the Clinical Research Ethics Committee of the University Clinical Hospital “Virgen de la Arrixaca” (Murcia, Spain) (ID: 2024-5-7-HCUVA, approval date: 28 May 2024). Participants are randomly assigned to one of two groups: (1) a supervised progressive resistance training program (SPoRT-PCa-ADT), or (2) a control group receiving a home-based exercise protocol following an initial assessment, accompanied by weekly telephone follow-up. Assessments are conducted at baseline, 12 and 24 weeks to examine changes in physical, functional, and psychosocial outcomes. Additionally, patient-reported outcomes are collected at the 12-week midpoint (Fig. 1). This study design enables the evaluation of both immediate and sustained intervention effects and facilitates a direct comparison between supervised and home-based exercise approaches, in line with methodological recommendations proposed by Galvão et al. [20].

**Fig. 1 Fig1:**
[figure not shown]
Patient Flowchart of the SPORT-PCa-ADT Program

The theoretical framework integrates progressive resistance training principles with specific considerations for ADT-induced physiological changes, including muscle loss, increased fat mass, and decreased bone mineral density. The program emphasizes velocity-based training methods, functional movement patterns, systematic progression accounting for treatment-related symptoms, and evidence-based assessment tools appropriate for this population, aligning with community-based exercise programs that have demonstrated effectiveness for cancer patients as described by Cormie et al. [21]. The program is implemented by the Never Surrender Foundation in collaboration with the Urology Department of the University Clinical Hospital “Virgen de la Arrixaca” in the Region of Murcia, Spain.

Any important modifications to the trial protocol (e.g., changes to eligibility criteria, outcomes, or statistical analyses) will require prior approval from the Clinical Research Ethics Committee of the University Clinical Hospital ‘Virgen de la Arrixaca’. Approved amendments will be updated on ClinicalTrials.gov (NCT07064811) and communicated to the research team and, where applicable, to enrolled participants. Participants whose continued trial participation is affected by an amendment will be re-consented using an updated consent form.

### Participants

#### Eligibility criteria

Male individuals of legal age diagnosed with locally advanced or metastatic prostate cancer and undergoing androgen deprivation therapy (ADT) are eligible for inclusion in this randomized controlled trial. The primary objective was to assess the impact of a structured physical exercise intervention on physical function, cancer-related fatigue, and quality of life in this patient population. Participants are randomly allocated to one of two groups: those in the intervention arm received supervised exercise in accordance with the SPoRT-PCa-ADT Program, while those in the control arm are provided with a home-based exercise regimen following an initial evaluation, supported by weekly telephone follow-ups.

The inclusion and exclusion criteria are presented in the Table 1, following the recommendations of previous randomized controlled trials to target an clinically homogeneous population, maximizing potential benefits and be consistent with exercise guidelines for cancer patients [8, 22].

**Table 1 Tab1:** Inclusion and exclusion criteria

Inclusion criteria	Male participants aged 18–80 years Diagnosis of locally advanced or metastatic prostate cancer Currently receiving androgen deprivation therapy (ADT) Treatment at Urology and oncology departments within the University Clinical Hospital “Virgen de la Arrixaca” healthcare network Legal capacity and signed informed consent Ability to attend supervised sessions or perform home-based exercises safely Physician clearance for exercise participation
*Exclusion criteria*	Unwillingness to participate in the study Inability to complete adequate follow-up Uncontrolled or symptomatic metastatic bone disease Physical disabilities that would prevent participants from safely completing the protocol Severe cardiovascular disease or contraindications to exercise determined by assessment Participation in structured resistance training within the previous 6 months Cognitive impairment limiting ability to follow exercise instructions Uncontrolled hypertension (> 160/100 mmHg) Active treatment for other primary cancers

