#### Randomization

Following eligibility confirmation and informed consent, all participants complete baseline assessments prior to randomization. Participants are randomly allocated to groups using a computer-generated randomization sequence with variable block sizes (4, 6, and 8) to ensure allocation concealment and prevent prediction of future allocations [27]. Randomization is stratified by age group (< 65 vs. ≥65 years) and ADT duration (< 12 vs. ≥12 months) to ensure balanced distribution of key prognostic factors that may influence treatment response. Age stratification accounts for potential differences in exercise adaptation between younger and older adults [28], while ADT duration stratification addresses the progressive nature of treatment-related side effects, as longer ADT exposure is associated with greater muscle mass loss and functional decline [29]. An independent researcher with no involvement in participant recruitment or assessment performs the randomization procedure using a secure online randomization system.

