### Exercise protocol of intervention group

The SPORT-PCa-ADT Program is designed following international guidelines on evidence-based exercise prescription for prostate cancer (PCa) patients undergoing ADT [13, 18]. The program is specifically tailored to counteract the well-documented adverse effects of ADT, including muscle loss, increased fat mass, decreased bone mineral density, and cancer-related fatigue. Particular attention was given to balancing physiological effectiveness with practical implementation considerations.

Subjects participate in the supervised exercise program twice weekly (with a 48–72-hour interval between sessions) for 24 weeks, totaling 48 supervised sessions. The progressive resistance training program uses velocity-based training principles [32–34], a novel approach in exercise oncology that allows for precise load management and individualization based on daily performance capacity [35]. The sessions are conducted in a specialized sports center under direct supervision of exercise physiologists and sports scientists specifically trained in the SPORT Protocol, at the same time of day (± 1 h) for each participant, and under controlled environmental conditions (20 °C and 60% humidity). The study protocol of exercise training and evaluation is shown in Fig. 2.

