### Statistical analyses

Statistical analyses will be performed using JAMOVI (version 2.5, The JAMOVI Project, Sydney, Australia). Descriptive statistics will be calculated for all variables, with data presented as means and standard deviations for continuous variables and frequencies and percentages for categorical variables. Graphical representations will be generated using GraphPad Prism (version 10, GraphPad Software Inc., San Diego, CA, USA).

The primary analysis will include all participants who completed both baseline and post-intervention assessments in their respective groups. Additional sensitivity analyses will be conducted using intention-to-treat principles, with missing data handled using multiple imputation by chained equations (MICE) with predictive mean matching for continuous variables. For all outcome measures, analysis of covariance (ANCOVA) will be used to compare post-intervention values between groups while adjusting for baseline values and stratification variables (age group and ADT duration).

Bonferroni post-hoc corrections will be applied for multiple comparisons across outcome measures. Effect sizes will be calculated using Cohen’s d for between-group differences and partial eta-squared for ANCOVA models, with values of 0.2, 0.5, and 0.8 considered small, medium, and large effects for Cohen’s d, respectively [45]. For all analyses, *p* < 0.05 will be considered statistically significant. Per-protocol analyses will be conducted as sensitivity analyses, including only participants with ≥ 85% adherence. Exploratory subgroup analyses will examine potential effect modification by baseline characteristics including age, ADT duration, and baseline functional status. Correlation analyses will examine relationships between changes in objective physical performance measures and patient-reported outcomes within each group.

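### The inclusion criterion on exercise ability is met by either ability alone, so a man can be randomised to an arm whose programme he cannot follow

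*Protocol article*

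**What the plan says.** In the protocol article, Table 1 (Eligibility criteria) requires "Ability to attend supervised sessions or perform home-based exercises safely". The text above the table states that "Participants are randomly allocated to one of two groups". The Randomization section gives the order of events: "Following eligibility confirmation and informed consent, all participants complete baseline assessments prior to randomization". The Blinding section adds that participants are told either assignment is equally possible.

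The supervised arm trains twice weekly "for 24 weeks, totaling 48 supervised sessions", and on place the same section says: "The sessions are conducted in a specialized sports center under direct supervision of exercise physiologists". The control arm trains at home from written instructions, with a weekly telephone call.

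The nearest related exclusions are "Physical disabilities that would prevent participants from safely completing the protocol" and "Inability to complete adequate follow-up". Physician clearance is also required; under Recruitment and screening it confirms that exercise is not contraindicated.

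On the analysis set, Statistical analyses says: "The primary analysis will include all participants who completed both baseline and post-intervention assessments in their respective groups". Intention-to-treat and per-protocol analyses (at least 85% adherence) are sensitivity analyses.

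**The concern.** In a randomised comparison, each participant must be able to receive whichever intervention the allocation gives him. A criterion satisfied by one of two abilities does not secure that. Applied literally, it admits a man who can only train at home, and half of such men would be expected to be allocated to the centre. It equally admits a man who can train under supervision but not safely on his own.

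Two things are at stake. If men who cannot follow their arm stay in the analysis, the contrast between arms is diluted and power is lost. If they also fail to return for the final assessment, the completer-based primary analysis drops them, and the losses concentrate in whichever arm they could not follow.

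**Working it through.** **1. Can the criterion mean the ability that matches the assigned arm?** No. Eligibility is confirmed, consent taken and baseline testing done before allocation, so a check made at entry cannot depend on the arm.

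**2. Does another criterion close the gap?**

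| Provision | What it covers | Capacity for 48 centre visits? |
|---|---|---|
| Physical-disability exclusion | Bodily capacity to complete safely | Not distance, transport or timetable |
| Follow-up exclusion | Completing follow-up | Physical assessments are at baseline and post-intervention only |
| Unwillingness exclusion | Consent | Not inability |
| Physician clearance | Contraindications to exercise | No |
| Baseline testing before randomisation | At least one visit; squat and jump performance | Not repeated attendance |
| Treatment within the hospital's network | Where care is given | Does not address travel |
| Flexible scheduling; transport help when feasible | Adherence after entry | Not an entry condition |

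These remove many men with physical limits. What remains is mainly logistical: men able to exercise but unable to reach the centre twice a week for 24 weeks.

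**3. Reproducing the planned size.** Inputs from Sample size: f = 0.25, α = 0.05, power 0.95, k = 2 groups, m = 3 measurements, ρ = 0.5, ε = 1, dropout 15%. For the repeated-measures within-between interaction:

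- λ = f² × N × m / (1 − ρ) = 0.0625 × 44 × 3 / 0.5 = 16.5
- df1 = (k − 1)(m − 1) = 2; df2 = (N − k)(m − 1) = 84
- Power = 95.6%, and 44 is the smallest even N reaching 95%
- 44 / 0.85 = 51.8, so 52 (26 per arm)

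The stated 44 and 52 reproduce and are not in dispute.

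**4. Dilution if the men stay in the analysis.** Assume that a share q of the supervised arm cannot attend and gains nothing over control. The effect becomes f(1 − q), so λ = 16.5 × (1 − q)². The documents give no q; the range is illustrative.

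| q | Men out of 26 | f(1 − q) | λ at N = 44 | Power at N = 44 | Evaluable N for 95% |
|---|---|---|---|---|---|
| 0 | 0 | 0.2500 | 16.50 | 95.6% | 44 |
| 5% | 1.3 | 0.2375 | 14.89 | 93.4% | 48 |
| 10% | 2.6 | 0.2250 | 13.37 | 90.6% | 54 |
| 20% | 5.2 | 0.2000 | 10.56 | 82.3% | 66 |

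This uses the protocol's own sample-size model to give a scale. Absolute power under the ANCOVA named in Statistical analyses would differ, but the factor (1 − q) on the effect would be the same.

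**5. Loss if the men also miss the final assessment.** If this comes wholly on top of the planned 15%, supervised completers = 26 × 0.85 × (1 − q) = 22.1 × (1 − q): about 21.0, 19.9 and 17.7 for q = 5%, 10% and 20%, against 22 planned. With overlap between q and the 15%, the shortfall is smaller.

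**The case against.** The best defence is that the wording is loose rather than wrong. It mirrors the description of the two arms; men are told that either arm is equally possible; and one who knew he could not attend would probably decline. The exclusions, physician clearance and Smith-machine and jump testing at baseline remove many less mobile men. They also make the reverse case uncommon: a man who passes that testing but cannot safely do low-effort box squats. The 15% dropout figure is taken from supervised exercise programmes, so it may already include some attendance failure.

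Much of this stands. It limits how many such men would enrol and is a reason to read the higher values of q with caution. It does not rescue the criterion, which is printed as a rule, is applied before the arm is known, and is backed by no other rule on repeated attendance.

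A reader might go further and infer that the primary analysis would lose men from the supervised arm alone and so favour supervised training. The documents do not support that. The primary set depends on completing assessments, not on attending sessions, so a non-attender who returns for the final test stays in. The criterion also admits the reverse case, which would cause losses in the home arm. And nothing in the documents shows that men who cannot travel have worse outcomes.

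**Conclusion.** The criterion should be corrected. As written, it allows enrolment of men who cannot receive one of the two interventions to which they may be allocated. The firm part is the logic of the wording set against the order of eligibility and allocation. The size is conditional: power at N = 44 falls by about 2 percentage points at q = 5%, 5 at q = 10% and 13 at q = 20%, if these men are retained and gain nothing over control. The share q is an assumption and may partly overlap the dropout allowance. Selective loss in the primary analysis needs the further assumption that non-attenders also miss the final assessment. It would then fall mainly on the arm they could not follow, with the direction of any bias unknown. Restricting the primary analysis to completers is a separate matter and adds no weight here.

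**What to change.** In Table 1, replace *or* with *and*, so that a participant must be able both to attend the supervised sessions for the full 24 weeks and to perform the home programme safely. Record both as confirmed before randomisation. The change goes through the ethics-committee amendment route already described under Design, with the registry entry updated. The cost is that amendment and slightly fewer eligible men; the transport help already planned may recover some of them. The planned 44 evaluable and 52 recruited participants do not change.
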